#### DSMB responsibilities

##### Primary

1. Regular (at least every 3 months) review of safety data and serious adverse events

2. Formal interim analyses of efficacy data

3. Feedback to the Operations Committee

##### Secondary

1. Respond to special requests from regulatory authorities or IRBs

2. Recommendations for protocol amendments

3. Verification of final analysis of the study will be done by the DSMB Associated Statistician

Recommendation to stop a trial early for safety reasons is, by definition, a qualitative judgment. The DSMB is composed of eminent clinicians and methodologists who are experienced with clinical trials and can be relied upon to exercise good judgment in weighing the potential risks and benefits to patients as data accumulate in this trial. Safety aspects and more specifically severe bradycardia, heart block, severe hypotension will be monitored. No formal boundaries will be proposed, but clear, consistent, and persistent evidence of net harm that overwhelms any benefit should be apparent. A recommendation to stop the trial will be based on the pattern of treatment effect across all endpoints, as well as the benefit/risk ratio.

The DSMB will fulfill its responsibility to monitor the safety of patients in CHARITY by conducting formal reviews of accumulated safety and efficacy data. These reviews will normally occur at regular intervals. The DSMB Associated Statistician will prepare a report of aggregate data summaries and individual patient data listings, where appropriate, for each treatment group. This report will be circulated to each member of the DSMB at least one week prior to their collective review. The committee will then convene, either by face-to-face meeting or by telephone conference call, to make its recommendation to the Operations Committee with respect to continuance of the trial. A formal written communication to the Chairman of the Operations Committee will then follow. Minutes of all official meetings of the DSMB will ultimately be part of the Sponsor's master files (archives). The report of data summaries and listings will include information on both safety and efficacy parameters, together with status reports designed to show the extent to which the trial is being executed according to protocol. Included among the safety data will be (a) all deaths and (b) adverse events. Efficacy summaries will provide information on the occurrence of study outcomes. The outcome events are considered as distinct from adverse events and summarized separately. At each review by the DSMB, consideration of a decision to stop the trial on grounds of patient safety will weigh the current evidence of differences between treatments regarding adverse effects (as expressed by mortality, adverse event reports, etc.) against emerging trends in efficacy. Providing efficacy data at each of these routine safety reviews does not constitute a formal interim analysis of efficacy. Blinded data for the safety review will be made available from the Central Study Database. Serious adverse events are required to be reported rapidly to the FCVRI Project Office and will be entered into a separate data base. These reports will be added to the data to be reviewed by the DSMB. Outcome events will be reviewed by the Event Adjudication Committee on an ongoing basis to determine if each reported event meets the defined criteria for a study outcome event. The DSMB will review data on all reported outcome events. Additional summaries will show the results of the Event Adjudication Committee's judgements on the subset of reports that has been reviewed by this committee. This committee is independent from the FCVRI and its responsibilities are to review the protocol and perform an interim analysis plan, review safety, efficacy, compliance and trial progress at 12 months after the first randomization and if requested by the Steering Committee. The Data and Safety Monitoring Board (DSMB) will make recommendations to the Steering Committee about any potential problems. Any major recommendation, e.g. amending the protocol or stopping the trial will be reviewed and ratified by the Steering Committee.

### Adverse Events and Adjudication Committee

The Event Adjudication Committee is charged with the responsibility for validating all reported primary fatal and nonfatal outcomes and validating the classification of cause of death. The Event Adjudication process will be coordinated at the FCVRI Project Office in Bucaramanga. This committee, composed of experts in the field will review, in a blinded manner; all reported outcome events to provide consistency and validity in the assessment of outcomes. Their decisions will be based on blind clinical data provided and they will consider the impressions of the clinical investigator. Their decisions will be used in the final analysis. Members of the Event Adjudication Committee will be chosen based on their clinical expertise. Adjudicators will be trained at a preliminary meeting where study definitions will be reviewed and test cases performed to ensure uniform application of study definitions. Reported events will be adjudicated by at least one committee member. Dossiers of reported events will be prepared and distributed to committee members on a regular basis to ensure that events are adjudicated in a timely fashion. Each committee member will be requested to review the dossiers and acknowledge in writing their agreement/disagreement with the investigator's interpretation of events.

The AE Committee (AE&AC) is composed by clinical experts and one principal investigator, its responsibilities are to review and verify every AE, SAE and Adverse Drug Reactions (ADR) reported, and to supervise all relevant SAE information is complete. The AE&EC will validate all SAE in a blinded form and notify investigators, Independent Ethics Committees and regulation authorities of all SAE and clinically relevant AE. The AE&EC will also validate outcomes providing standard classifications and definitions and reviewing supporting information provided by investigators.

### Safety assessment

Safety assessment will consist of monitorization of all adverse events, serious adverse events and protocol outcomes. Physical exam including sitting and standing blood pressures, heart rate and presence of CHF signs will be measured and recorded in the case report form (CRF). During visit 4, the security visit, an ECG will be recorded to assess heart rate and presence of conduction disturbances before proceeding to dispense medication.

### Adverse events

All adverse events informed by the subjects, detected by the investigators or detected through physical examination will be recorded in the individual' s CRF and reported to the principal investigators within the next five days.

An adverse Event (AE) is any untoward or undesirable medical occurrence in a subject that does not necessarily have a causal relationship with the study treatment medication. An AE can be any symptom, sign or medical condition occurring after starting the study drug whether it corresponds to bisoprolol or placebo. Medical conditions present before starting the study are considered AE only if they worsen after starting the study treatment. An abnormal laboratory finding not present before starting the study treatment is also considered an AE and should be recorded in the CRF.

The Adverse Events is described in the CRF Adverse Events form (CRF 50) including date and duration, severity (mild, moderate, severe, only laboratory abnormality), relation with the study drug (suspected, not suspected), action taken (none, drug discontinued, dose adjustment, drug interruption, hospitalization, withdrawal) and outcome of the event (recovery, persistent problem, sequelae, death). All fields requested in the AE form must be filled and submitted to the AE committee.

### Effects of Bisoprolol

The known effects and tolerability to bisoprolol will be monitored in each visit; any intolerability or negative change in vital signs will be recorded as an AE. The following definitions apply to the side effects associated with Bisoprolol independent of the study' s endpoints.

1. Bradycardia: Bradycardia is defined as a frequency of <45 beats per minute detected by pulse palpation, cardiac auscultation or ventricular frequency in an ECG.

2. Hypotension: Hypotension is defined as a sitting systolic blood pressure < 100 mmHg or a sitting diastolic blood pressure < 60 mmHg. The investigator must sate whether hypotension is asymptomatic or symptomatic.

3. Orthostatic hypotension: Orthostatic hypotension is a decrease in systolic or diastolic blood pressure of ≥20 mmHg or ≥10 mmHg respectively. The investigator must sate whether orthostatic hypotension is asymptomatic or symptomatic.

4. Fatigue: Fatigue is described as a perceived sensation of weakness during ordinary physical activities not present before starting the study treatment drug.

5. Bronchospasm: Bronchospasm is defined as bronchial wheezing during auscultation or wheezing perceived by the subject during respiratory symptoms of cough or dyspnea.

6. Cold extremities: Cold extremities are defined as the sensation of coldness in digits, hands or feet not present before starting the study drug.

### Serious Adverse Events

Serious Adverse Event (SAE) is any untoward medical occurrence that at any dose of the study drug results in:

1. Death

2. Is life-threatening

3. Requires hospitalization or prolongation of existing hospitalization

4. Results in persistent or significant disability

5. Results in congenital anomaly at birth

SAE will be recorded in the CRF SAE form and reported to the principal investigator at FCV within 24 hours of learning of its occurrence. The SAE form requires information about date, medical diagnosis, consequences and severity (fatal, life-threatening, requiring hospitalization, disability/incapacity, birth defects or other consequence), date of hospitalization, date of death, study treatment drug dose, date of first dose, date of dose adjustment, relationship with the study treatment drug (suspected, not suspected) and study withdrawal of the subject (yes or no). The SAE form must be signed by the principal investigator and the study monitor.

All SAE will be followed until their resolution or the completion of the trial. Follow-up will be recorded in the CRF SAE follow-up (CRF52) form stating the subject' s outcome as resolved, dead, lost to follow-up or unknown. Hospitalization SAE should include copy of the summary epicrisis from the corresponding hospital or clinic. All SAE follow-up forms must be signed by the principal investigator and the study monitor.

SAE which constitute endpoint according to the protocol' s definitions, will be recorded additionally in the CRF corresponding endpoint form. Each endpoint has its own CRF page which must be submitted to the AE committee for validation.

Events not considered SAE are hospitalization for:

1. Routine treatment or pre-scheduled hospitalizations for heart failure not associated with any clinical deterioration.

2. Elective or scheduled treatment for pre-existing conditions that did not worsen during the study.

### Statistical methods

Descriptive statistical analysis will be composed with simple distribution of frequencies, calculation of proportions, means, their respective standard deviations and 95% confidence intervals. For effects of group comparison, t-test and Mann-Whitney tests will be used according to the dependent variable distribution. For categoric variables, the Chi-square test or the exact Fisher test will be applied as corresponding. Patient survival and hospitalization rates will be described using Kaplan-Meijer estimates and survival graphs. Cox regression will be used for the multivariate analysis of time to death and time to hospitalization. Formal efficacy interim analyses will take place one year after the recruitment phase.

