## Abstract

**Background:**

Chagas' disease is the major cause of disability secondary to tropical diseases in young adults from Latin America, and around 20 million people are currently infected by *T. cruzi*. Heart failure due to Chagas cardiomyopathy is the main clinical presenation in Colombia. Heart failure due to Chagas' disease may respond to digoxin, diuretics and vasodilator therapy. Beta-adrenoreceptor antagonism seems to protect against the increased risk of cardiac arrhythmia and sudden death due to chronic sympathetic stimulation. The aim of this study is to evaluate the effects of the selective beta-adrenergic receptor blocker Bisoprolol on cardiovascular mortality, hospital readmission due to progressive heart failure and functional status in patients with heart failure secondary to Chagas' cardiomyopathy.

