**Methods/design:**

A cohort of 500 *T. cruzi *seropositive patients (250 per arm) will be selected from several institutions in Colombia. During the pretreatment period an initial evaluation visit will be scheduled in which participants will sign consent forms and baseline measurements and tests will be conducted including blood pressure measurements, twelve-lead ECG and left ventricular ejection fraction assessment by 2D echocardiography. Quality of life questionnaire will be performed two weeks apart during baseline examination using the "Minnesota living with heart failure" questionnaire. A minimum of two 6 minutes corridor walk test once a week over a two-week period will be performed to measure functional class. During the treatment period patients will be randomly assigned to receive Bisoprolol or placebo, initially taking a total daily dose of 2.5 mgrs qd. The dose will be increased every two weeks to 5, 7.5 and 10 mgrs qd (maximum maintenance dose). Follow-up assessment will include clinical check-up, and blood collection for future measurements of inflammatory reactants and markers. Quality of life measurements will be obtained at six months. This study will allow us to explore the effect of beta-blockers in chagas' cardiomyopathy.

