### Pretreatment considerations

Baseline vital signs will be obtained with patients in the sitting and after 3 minutes in the standing position.

Twelve-lead ECGs will be recorded in each patient.

Left ventricular ejection fraction at rest will be determined by echocardiography, using a modified Simpson's rule to calculate LV volumes.

Quality of life questionnaire will be administrated two weeks apart during baseline examination using a translated-validated version of the "Minnesota living with heart failure" questionnaire.

Minimum of two 6-minutes corridor walk test once a week over a 2-week period will be performed. The last value will be used if it is within 10% of the previous value.

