### Follow-up period

ECG tracings will be recorded during the security visit and at 1 and 2 years.

Patients will be followed for two years after randomization.

Repeat echocardiograms will be recorded at 1 and 2 years of follow-up along with HF Quality of-life questionnaire and six-minute walk tests.

Clinical measurements will be obtained every three months along with an assessment of treatment adherence and tolerance. Mortality and hospitalization events will be ascertained by telephonic interview and verified with hospital charts review, up to two years after randomization.

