### Secondary efficacy outcomes

Secondary outcomes are the occurrence of any of the following:

1. Non-cardiovascular death.

2. Heart failure worsening or mortality related with CHF.

3. New AV block.

4. Need for Implantable cardioverter-defibrillator (ICD), Cardiac resynchronization Therapy (CRT) or Pacemaker therapy (PM).

5. Perceived quality of life worsening.

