### Endpoint definitions

1. Cardiovascular death: any death attributable to a cardiac or vascular cause occurring within two years after randomization.

2. Non-cardiovascular death: death from any cause excluding cardiovascular diseases occurring within two years after randomization.

3. Hospital admission/hospitalization caused by heart failure: admission in a hospital or clinic during at least 24 hours caused by heart failure worsening. It excludes procedures and hospitalization for procedures which have been scheduled and not due to worsening of the current heart failure condition since randomization.

4. Heart failure worsening: decline of at least one functional class as defined by the New York Heart Association occurring during any inter- visit period of three months needing inotropic support, IV diuretics, medication dose adjustments or additional drugs for compensation.

5. Perceived quality of life worsening: increase in the "Minnesota living with heart failure" test score of at least 10 points. The test' s score ranges from 0 (best) to 100 (worst).

6. New AV block: appearance of any AV conduction disturbance including first, second and third degree AV block after randomization.

7. Bradycardia requiring pacemaker implantation: ventricular rates < 50 per minute due to any cause including sick-sinus syndrome and AV block, causing symptoms or disability and complying with current indications for permanent pacemaker implantation.

8. ICD: Implantable cardioverter-defibrillator indicated for the prevention and treatment of sudden death, ventricular tachycardia/ventricular fibrillation.

9. CRT: cardiac resynchronization therapy or biventricular pacing or ventricular bifocal pacing for the treatment of advanced heart failure.

10. PM: permanent pacemaker for the treatment of conduction disturbances.

11. Clinically significant ventricular arrhythmias: sustained monomorphic ventricular tachycardia or ventricular fibrillation with symptoms caused by hemodynamic or perfusion alterations, circulatory collapse or syncope.

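### Quality of life is fixed only as a yes/no worsening of 10 points, with no baseline-adjusted analysis of the score, and its assessment times conflict

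*Protocol article*

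**What the plan says.** The Secondary objective section names quality of life. Under Secondary efficacy outcomes it appears once, as "Perceived quality of life worsening". Endpoint definitions makes this a rise in the Minnesota "test score of at least 10 points", on a scale from 0 (best) to 100 (worst).

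At baseline, under Pretreatment considerations, "Quality of life questionnaire will be administrated two weeks apart during baseline examination". Ejection fraction and six-minute walk distance are also measured at baseline.

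Two places give the follow-up timing:
- Abstract, Methods/design: "Quality of life measurements will be obtained at six months".
- Follow-up period: "Repeat echocardiograms will be recorded at 1 and 2 years of follow-up along with HF Quality of-life questionnaire and six-minute walk tests".

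On analysis, Statistical methods says: "For effects of group comparison, t-test and Mann-Whitney tests will be used according to the dependent variable distribution". Categorical variables go to chi-square or Fisher's exact test. The only multivariable model named is Cox regression, for time to death and time to hospitalization.

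**The concern.** A score from 0 to 100 carries much more information than whether it rose by 10. Under the cut, a patient who worsens by 9 points, one who is unchanged and one who improves by 30 all count alike. The section on the consequences of Chagas' disease cites improved quality of life among the reported effects of beta-blockade, yet the listed outcome gives no credit for improvement beyond not having worsened. Baseline score usually predicts follow-up score, so adjusting for it gains precision from data the trial already plans to collect.

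The timing conflict is a separate problem. It concerns which forms are handed out as well as how they are analysed, and no analysis plan can recover a questionnaire that was never given. The definition of worsening names no visit, so it does not settle which schedule applies.

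At stake is whether the trial can say anything useful about quality of life.

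**Working it through.** **The plan's own figure.** The protocol plans 500 patients, 250 per arm, and gives a 30% relative reduction for the composite. It gives no power, SD or target difference for quality of life, so there is no figure to reproduce on this point.

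**Assumed inputs (none from the documents).** True difference d = 5 points in favour of bisoprolol; mean change 0 on placebo; SD of the score s = 20; baseline/follow-up correlation r = 0.5; normal change scores; two-sided 5% test; 200 evaluable per arm (80% of 250).

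**Standard deviations.**
- Change score: s × √(2(1 − r)) = 20 × √1 = 20.
- ANCOVA residual: s × √(1 − r²) = 20 × √0.75 = 17.32.

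**Power with 200 per arm.**
- Yes/no outcome: P(rise ≥ 10) is 1 − Φ(10/20) = 0.309 on placebo and 1 − Φ(15/20) = 0.227 on bisoprolol. A two-proportion comparison has power of about 46%.
- t-test on change: standard error 20 × √(2/200) = 2.0; Φ(5/2.0 − 1.96) = Φ(0.54), about 71%.
- ANCOVA: standard error 17.32 × √(2/200) = 1.732; Φ(5/1.732 − 1.96) = Φ(0.93), about 82%.

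**Range of assumptions, 250 per arm, no loss, d = 5.** The middle columns give power. The last three give the sample per arm for 80% power and the ratio of the two.

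| SD | r | Yes/no | t, follow-up score | t, change | ANCOVA | n yes/no | n ANCOVA | Ratio |
|---|---|---|---|---|---|---|---|---|
| 20 | 0.3 | 43% | 80% | 66% | 83% | 614 | 229 | 2.7 |
| 20 | 0.5 | 54% | 80% | 80% | 90% | 458 | 189 | 2.4 |
| 20 | 0.7 | 72% | 80% | 95% | 98% | 304 | 129 | 2.4 |
| 25 | 0.3 | 31% | 61% | 47% | 65% | 923 | 358 | 2.6 |
| 25 | 0.5 | 40% | 61% | 61% | 73% | 678 | 295 | 2.3 |
| 25 | 0.7 | 57% | 61% | 82% | 88% | 434 | 201 | 2.2 |

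In every row the yes/no outcome has the lowest power and ANCOVA the highest.

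**Time points side by side.** The abstract gives six months and no later assessment. The follow-up section gives 1 and 2 years and no six-month assessment. Neither mentions the other schedule, and the definition of worsening does not choose between them.

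**The case against.** A 10-point threshold fixed in advance is a legitimate responder definition, and unadjusted two-sample tests are valid in a randomised trial. This is a condensed article, and an analysis plan that is not shown could add an adjusted model. The power figures rest wholly on assumed inputs. They also ignore death: a continuous analysis covers only patients alive with a score, whereas a yes/no outcome can count deaths as worsened, so the comparison is not quite like for like. Quality of life is the last of five secondary outcomes.

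All of this stands, and it limits the weight of the point. It does not remove the point, because the protocol itself fixes the outcome as a cut score and itself gives two schedules.

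Three stronger readings are tempting, and the document does not support them:
- *The plan throws its baselines away.* It does not. A rise of 10 points is measured from a baseline, although the article does not say which of the two baseline questionnaires is the reference. The t or Mann-Whitney test could also be run on change.
- *Choosing between t and Mann-Whitney from the data leaves the quality-of-life estimand open.* That sentence does not govern the listed outcome, which is categorical. It could apply to walk distance or ejection fraction, but neither is a listed outcome.
- *Functional status is in the stated aim but has no outcome.* The abstract's aim does include "hospital readmission due to progressive heart failure and functional status", but heart failure worsening, defined partly by a drop in NYHA class, covers it in part. Adding walk distance or ejection fraction as outcomes would be a preference.

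**Conclusion.** The point holds for a secondary outcome and is worth correcting. As written, quality of life is analysed only as a 10-point worsening, and no baseline-adjusted model is named for any continuous measure. Under the assumed inputs the loss is large: about 46% power against 82% for ANCOVA with 200 per arm. The sizes are illustrative; the ranking held in every scenario run.

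The conflict between six months and 1 and 2 years depends on no assumption and must be reconciled. A reader might infer that two schedules are there so that the more favourable can be reported. Nothing in the document shows that intent; it shows only that the schedule is not settled.

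**What to change.** 1. Analyse the Minnesota score as a continuous outcome, by ANCOVA or a repeated-measures model with baseline as covariate. State the reference baseline, for example the mean of the two baseline questionnaires.
2. Keep worsening of at least 10 points as a supporting responder analysis, with a sensitivity analysis that counts deaths as worsened.
3. Reconcile the abstract with the Follow-up period section to one questionnaire schedule, and name one primary time point for quality of life.
4. If walk distance or ejection fraction is compared between arms, use the same baseline-adjusted model.

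The cost is wording in the protocol or analysis plan and slightly more analysis work. No new data are needed if the schedule at 1 and 2 years stands; keeping a six-month assessment as well would add one questionnaire. The continuous analysis describes only patients alive with a score, which is why the sensitivity analysis in step 2 should accompany it.

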Congestive heart failure (CHF) is a late manifestation of CD that results from structural abnormalities and extensive and irreversible damage to the myocardium. Heart failure in *T. cruzi *infected patients usually occurs after age 40 and follows AV block or ventricular aneurysm. However, when CHF develops in patients less than 30 years old it is frequently associated with a more aggressive myocarditis and an extremely poor prognosis [1]. The mortality attributable to CD is related to the severity of the underlying heart disease. Very high mortality is often found in patients with CHF [2], however, mortality in asymptomatic seropositive patients varies greatly between geographic regions, suggesting that other factors may influence the severity and progression rate of cardiac disease. It is believed that cardiac damage in CD progresses slowly but steadily over decades, from subclinical myocarditis to mild segmental abnormalities with conduction defects, to severe ventricular structural abnormalities, and finally to overt congestive heart failure and sudden cardiac death. Besides the poor prognosis of CHF due to Chagas' disease, it is important to estimate the risk of complications and death in patient infected with *T. cruzi*. Unfortunately, few clinical studies have addressed this issue. Most *T. cruzi *infected patients have mild or no clinical disease, however, the percentage of infected people that will develop detectable cardiac abnormalities is approximately 30 to 40% [3], but only 20% of them will develop symptomatic cardiac involvement [6]. Like CHF from other causes, CHF due to CD responds to digital, diuretics and vasodilators therapy [7]. Additionally, some studies have shown that angiotensin-converting enzyme (ACE) inhibitors improve survival in patients with moderate to severe CHF due to CD [8]. In spite of its benefits on patients with non Chagas' disease CHF, there is considerable uncertainty about the potential role of ACE inhibitors in patients with CHF due to Chagas' disease. *Captopril*, and ACE inhibitors, has been shown to reduce neurohormonal activation and non-lethal arrhymias in a small number of patients with Chagas' heart failure [8,9].

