Beta-blockers already proven to be beneficial in CHF patients are metoprolol, bisoprolol and carvedilol, drugs which have been tested in over 10.000 patients in more than 20 placebo-controlled clinical trials enrolling men and women with systolic dysfunction due to ischemia, hypertension and dilated idiopathic cardiomyopathy. Bisoprolol is a beta-1 selective blocker with the highest selectivity for this receptor, in doses less than 10 mg it has very little or no effect on beta-2 receptors. Bisoprolol was first tested in CHF in the CIBIS I trial which enrolled 641 patients and showed improvement in functional class, less hospitalizations for heart failure and a trend to improved survival. The much larger randomized CIBIS II assigned 2647 patients with class III or IV HF and an LVEF <40 percent to bisoprolol or placebo; the patients also received standard therapy with diuretics and ACE inhibitors. After an average follow-up of 1.4 years, the trial was prematurely stopped when the benefits were observed in the active treatment group: significant reduction in total all-cause mortality (11.8 versus 17.3 percent] that was independent of the severity or cause of HF. This benefit was primarily due to a reduction in SCD (3.6 versus 6.3 percent, p < 0.001], with a non-significant trend toward fewer deaths from HF; significant 15 percent reduction in hospital admissions for any cause and a 30 percent reduction in admissions for HF (p < 0.0001). Considering all the beneficial effects beta-blockers in patients with mild to severe CHF due to ischemic and non ischemic disease, there is no data regarding its potential effects in patients with CHF due to Chagas' disease. Based on the aforementioned we propose to develop a multi-center placebo controlled clinical trial to evaluate the effect of *Bisoprolol *in patients with CHF due to CD.

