### Expected impact

We expect that Bisoprolol in patients with CCM will determine a 30% relative risk reduction in mortality and morbidity. In the long term, we expect that this project will contribute to reduce the impact of the CCM and the health burden on the Colombian's health care system, particularly related with HF secondary to CCM.

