### Hypotheses

1. Bisoprolol will reduce cardiovascular death in patients with Chagas' cardiomyopathy with heart failure functional class NYHA II to IV.

2. Bisoprolol is safe in patients without advanced heart block.

3. Bisoprolol will significantly reduce hospitalization rates due to heart failure in patients with Chagas' cardiomyopathy in functional class NYHA II to IV.

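### The separate Kaplan-Meier curve for hospitalization, as naturally read, censors deaths and so overstates the probability of heart failure admission in both arms; a cumulative incidence curve should replace it.

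*Protocol article*

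**What the plan says.** The Statistical methods section gives one descriptive method for two outcomes: "Patient survival and hospitalization rates will be described using Kaplan-Meijer estimates and survival graphs". The next sentence again keeps them apart: "Cox regression will be used for the multivariate analysis of time to death and time to hospitalization". The section names no competing-risk method and does not say what happens to a patient who dies before being admitted.

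Heart failure hospitalization is a hypothesis of its own (Hypotheses, item 3: "Bisoprolol will significantly reduce hospitalization rates due to heart failure"), and it appears in the primary objective beside survival. Item 1 of the same list is "Bisoprolol will reduce cardiovascular death in patients with Chagas' cardiomyopathy", and the Expected impact section anticipates a "30% relative risk reduction in mortality and morbidity". The primary outcome is a first-event composite that includes both cardiovascular death and heart failure admission. Non-cardiovascular death is a secondary outcome.

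On how common death will be, the Background says "Very high mortality is often found in patients with CHF" but gives no figure for Chagas patients. Its only mortality figures come from the earlier large bisoprolol trial, CIBIS II: "significant reduction in total all-cause mortality (11.8 versus 17.3 percent", "After an average follow-up of 1.4 years".

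**The concern.** Death before admission makes a first admission impossible. A Kaplan-Meier curve for hospitalization alone has no event to record for such a patient, so in its standard form it censors the patient at death. The estimator then treats the dead as if they kept the same admission risk as the survivors. One minus that curve is the admission probability in a hypothetical world without death, not the proportion of patients who are admitted.

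The gap grows with mortality, so it matters in a population whose mortality the article calls very high. If fewer patients die on bisoprolol, the gap is wider on placebo, and the vertical distance between the curves exceeds the true difference in admission risk. At stake is the absolute picture that readers take from the display supporting hypothesis 3. The test of the primary outcome is not at stake.

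**Working it through.** **The plan's own figure.** The article gives no admission rate and no death rate for this trial, so there is no stated figure to reproduce. The check needs assumptions, which are listed here.

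**Inputs**
- Control mortality, from the Background: 17.3% over 1.4 years. As a constant hazard, d = −ln(1 − 0.173)/1.4 = 0.1357 per year, which is 1 − exp(−2 × 0.1357) = 23.8% at 2 years. These are not Chagas patients.
- Effect on death: 11.8% over 1.4 years gives −ln(1 − 0.118)/1.4 = 0.0897 per year. The hazard ratio is 0.0897/0.1357 = 0.66. The crude ratio 11.8/17.3 is 0.68. The protocol's 30% reduction corresponds to 0.70.
- Effect on admission: hazard ratio 0.70, from the protocol's 30%.
- Admission rate: assumed.
- Horizon: t = 2 years, from the Follow-up period section.

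**Formulas** (constant, independent hazards; h = admission, d = death)
- One minus Kaplan-Meier, deaths censored: 1 − exp(−h·t)
- Cumulative incidence: h/(h + d) × [1 − exp(−(h + d)·t)]

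**Example A: assumed 20% annual admission risk**, h = −ln(0.8) = 0.2231
- Control, Kaplan-Meier: 1 − exp(−0.4463) = 36.0%
- Control, cumulative incidence: (0.2231/0.3588) × [1 − exp(−0.7176)] = 0.6219 × 0.5121 = 31.8%
- Bisoprolol, with 0.70h = 0.1562 and 0.68d = 0.0923: Kaplan-Meier 1 − exp(−0.3124) = 26.8%; cumulative incidence (0.1562/0.2485) × [1 − exp(−0.4969)] = 24.6%
- Difference: 9.2 points by Kaplan-Meier against 7.2 by cumulative incidence, a ratio of 1.27. With a death hazard ratio of 0.66 or 0.70 the ratio is 1.28 or 1.26.

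**Example B: assumed 30% for both 2-year Kaplan-Meier admission and 2-year mortality, both hazard ratios 0.70**
- Control: 30.0% against 25.5%. Bisoprolol: 22.1% against 19.7%.
- Difference: 7.9 against 5.8 points, a ratio of 1.35.
- A simulation with 1,000,000 patients per arm gave the same percentages.

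**Range.** Control 2-year admission (one minus Kaplan-Meier) 20–40%, control 2-year mortality 20–40%, admission hazard ratio 0.70:

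| Death hazard ratio | Kaplan-Meier difference ÷ cumulative incidence difference |
|---|---|
| 0.7 | 1.21–1.54 |
| 1.0 | 1.10–1.26 |
| 1.3 | 1.01–1.08 |
| above about 1.33–1.47 | below 1 (benefit understated) |

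At a death hazard ratio of 0.7, Kaplan-Meier exceeds cumulative incidence by 2.0–8.0 points in control and by about 1 to 4.5 points on bisoprolol. The excess within each arm is present at every death hazard ratio; only the effect on the difference changes direction.

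**No effect on admission.** With an admission hazard ratio of 1, a death hazard ratio of 0.7, control 2-year admission of 30% by Kaplan-Meier and control mortality of 20–40%, Kaplan-Meier shows a difference of zero. Cumulative incidence shows 0.8–1.6 points more admissions on bisoprolol, because more patients survive to be admitted.

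**Primary composite.** Only non-cardiovascular death competes with it. If 10–20% of deaths are non-cardiovascular, the difference between arms changes by at most about 0.4 points.

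**The case against.** **The article does not say that deaths are censored.** It is a condensed account, and a fuller protocol or analysis plan might define the handling of death. That stands as a limit: censoring is an inference. But the point rests on the method that the article names for hospitalization, and in its standard form that method does censor these deaths.

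**The curves are descriptive and the model is Cox.** This stands. The Cox estimate for time to admission, with deaths censored, is a valid cause-specific hazard ratio. It needs a label, not a repair.

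**The two-year proportion may be available anyway.** The same section plans simple proportions, and the Follow-up period section ascertains deaths and hospitalizations to two years. With complete follow-up, the crude proportion admitted equals the cumulative incidence at that point. This also stands, but the published curve would then disagree with the tabulated proportion.

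**Stronger readings that the document does not support**
- A reader might infer that the plan is biased in favour of bisoprolol. The direction depends on the effect on death, which the trial is testing. If admission is unaffected, Kaplan-Meier does not create an apparent benefit.
- A reader might infer that the primary result is compromised because heart failure admission is one of its components. The composite counts cardiovascular death as an event, so most of the competing risk is already inside it.
- A reader might infer that a wrong number needed to treat will be reported. The article plans no absolute risk reduction or number needed to treat from these curves.

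**Conclusion.** The point holds in a limited form. A Kaplan-Meier curve for hospitalization, with deaths censored, displays the wrong quantity and overstates the admission probability in both arms. That part does not depend on the assumed rates. Its size does: about 4 points in control (36.0% against 31.8%) in Example A.

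The inflated absolute difference is conditional. It follows if the protocol's own expectations are met, shrinks if mortality is unchanged, and reverses if mortality rises enough, as the table shows. All these sizes rest on assumed admission rates, on mortality that is either assumed or taken from a non-Chagas trial, and on constant independent hazards.

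This is a correction worth making to a descriptive display for a named hypothesis. It does not threaten the Cox comparison or the primary analysis.

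**What to change.** In the Statistical methods section, or in the analysis plan if one is in use:
- For the separate heart failure hospitalization curve (hypothesis 3), replace Kaplan-Meier with the Aalen-Johansen cumulative incidence function, by arm, with death from any cause as the competing event.
- State that the Cox estimate for time to admission is a cause-specific hazard ratio with deaths censored. Showing it beside the hazard ratio for cardiovascular death or heart failure admission would help interpretation.
- Keep Kaplan-Meier for all-cause survival.

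The cost is a few sentences and standard software. The Serious Adverse Events section already provides for recording dates of death and of hospitalization, so no new data, visits or patients are needed.
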